## Abstract

**Introduction:**

The treatment of comorbid post-traumatic stress disorder (PTSD) and alcohol use disorder (AUD) is significantly more challenging than the treatment of either disorder alone. While gold standard evidence-based treatments exist for this comorbidity, clinically significant improvements are only observed in approximately half of clinical trial participants. The use of adjunctive pharmacotherapies, such as 3,4-methylenedioxymethamphetamine (MDMA), may serve to optimise gold standard interventions. The primary aim of the MDMA-assisted PTSD and Alcohol Therapy Trial study is to examine the therapeutic and cost-effectiveness of combining MDMA with evidence-based integrated care for comorbid PTSD+AUD. Specifically, we will examine MDMA-assisted integrated exposure therapy versus active control-assisted integrated exposure therapy in improving treatment outcomes for PTSD+AUD.

**Methods and analysis:**

This world-first double-blind trial will aim to randomise 100 participants with PTSD+AUD to a regimen of Concurrent Treatment of PTSD and Substance Use Disorders Using Prolonged Exposure (COPE) (12 sessions)+MDMA (80–160 mg: 2 dosing and 2 integration sessions) or COPE (12 sessions)+active control (niacin 250 mg: 2 dosing sessions and 2 integration sessions). All participants will receive medical management. The primary PTSD outcome will be the clinician-administered PTSD Scale for DSM-5. The primary drinking outcome will be the number of heavy drinking days (HDDs) per week, validated by phosphatidylethanol. Secondary PTSD and alcohol-related outcomes will include PTSD checklist for DSM-5 scores, absence of any HDDs and standard drinks per drinking day. We will also examine change in other clinical conditions and symptoms including depression, sleep disturbances and post-traumatic cognitions; treatment satisfaction and engagement; adverse events; and cost-effectiveness.

**Ethics and dissemination:**

This study will be conducted in accordance with the ethical principles outlined in the Declaration of Helsinki and the International Conference on Harmonisation-Good Clinical Practice guidelines. Ethical approval has been granted by the Sydney Local Health District Ethics Review Committee (X22-0121 & 2022/ETH00773). The results of this study will provide world-first data regarding safety, efficacy and cost-effectiveness of MDMA to optimise integrated exposure-based therapy for comorbid AUD and PTSD and will be disseminated to ensure wide accessibility and to support further research and clinical application.

**Trial registration number:**

NCT05709353.

STRENGTH AND LIMITATIONS OF THIS STUDYA strength of the MDMA-assisted PTSD and Alcohol Therapy Trial (MPATHY) trial is that it targets a common and challenging comorbidity (post-traumatic stress disorder (PTSD) with comorbid alcohol use disorder) that is not addressed in the majority of other 3,4-methylenedioxymethamphetamine (MDMA)-assisted therapy trials for PTSD.The MPATHY trial will minimise bias due to the use of the gold standard objective biomarker phosphatidylethanol to validate alcohol consumption data.The MPATHY trial will minimise bias due to the randomised and double-blind design in addition to the inclusion of an active control and prospective stratification for expectancy.The MPATHY trial is that it leverages an evidence-based behavioural intervention with strong empirical support for all participants.A potential limitation of this trial is the comprehensive nature of the evidence-based intervention combined with MDMA which may be resource intensive.

## Introduction

 Alcohol use disorder (AUD) is among the most prevalent and burdensome mental health conditions worldwide.^1^ For approximately 30%–40% of treatment-seeking individuals with AUD, the course of their illness, and attempts at recovery from AUD, are complicated by comorbid post-traumatic stress disorder (PTSD),^2^ a chronic and debilitating disorder that may develop following exposure to extreme trauma such as combat, sexual and physical assault, disasters and life-threatening accidents.^3^ This rate is alarmingly high when compared with the general population prevalence of 4%.^4^ The elevated prevalence of PTSD among people with AUD, and vice versa, is of considerable clinical concern due to the profound social, health and economic consequences of this comorbidity. Individuals with this comorbidity can often experience a more severe and complex form of PTSD characterised by extensive trauma histories, substantial clinical impairment,^5^ poor prognosis, psychosocial problems, substantially elevated suicide risk^6^ and high treatment attrition^7^ when compared with people with either disorder alone. Clinicians also view the treatment of this common comorbidity to be significantly more challenging than the treatment of either disorder alone.^8^

Underlying the relationship between these disorders are neural substrates common to both AUD and PTSD, including dysregulation of the body’s biological stress response system involving the hypothalamic-pituitary-adrenal axis and the noradrenergic/sympathetic system.^9^ In many cases, the AUD develops, and is maintained by, repeated attempts to ‘self-medicate’ PTSD symptoms^10^; in particular symptoms of avoidance and/or hyperarousal. Although alcohol use may provide short-term relief from symptoms by inhibiting central noradrenergic activity and its associated arousal states,^11^ growing tolerance to its effects leads to increasing use to obtain sufficient PTSD symptom reduction. In the absence of alcohol, PTSD symptoms may worsen, making it difficult, and in many cases impossible, for those experiencing these conditions to maintain abstinence or reduced use. Thus, once established, a cyclical relationship is formed whereby both disorders serve to maintain and exacerbate the other, leading to a chronic course of illness and significant treatment complications. Siloed approaches to the treatment of AUD and PTSD, whereby each disorder is treated sequentially, are largely ineffective.^12^

Systematic reviews and meta-analyses point to the safety and efficacy of integrated treatments that combine exposure-based cognitive behavioural therapies (CBTs) for AUD and PTSD.^13^,^15^ The approach with the most evidence to date is Concurrent Treatment of PTSD and Substance Use Disorders Using Prolonged Exposure (COPE).^16^ COPE combines prolonged exposure therapy to treat PTSD (imaginal exposure to trauma-related memories and in vivo exposure to avoided situations) with treatment components for alcohol use such as motivational enhancement therapy (eg, improving motivation) and CBT (eg, exploring how thoughts affect our behaviour, challenging maladaptive cognitions, managing cravings). Several randomised controlled trials (RCTs) have demonstrated that COPE is safe and effective in producing substantial reductions in both PTSD and AUD symptom severity, even among individuals with complex trauma histories and severe substance use disorders.^17^,^20^ COPE was designated as a first-line treatment for PTSD and substance use disorders by the American Psychological Association.^21^ Yet even when provided gold standard care such as COPE, only about half of participants in clinical trials demonstrate clinically significant improvements.^15 22^ Impediments to achieving optimal outcomes include difficulties engaging with critical components of exposure therapy, such as the capacity to recall, emotionally and cognitively engage with and process traumatic memories. The use of adjunctive pharmacotherapies may serve to unlock these barriers and optimise gold standard interventions^23^ through activation and deactivation of common neural pathways and has been identified as a priority by the International Society for Traumatic Stress Studies.^24^

In particular, 3,4-methylenedioxymethamphetamine (MDMA) is a promising candidate pharmacotherapy for augmenting COPE. MDMA raises levels of monoamine neurotransmitters in the brain (serotonin, norepinephrine, dopamine) and hormones (oxytocin, cortisol) leading to enhanced mood and increased feelings of trust and closeness to others,^25^,^28^ which may potentiate a stronger therapeutic alliance between client and clinician which is essential to all psychotherapies and may be particularly helpful in the context of PTSD and substance use.^29 30^ By reducing activation in the amygdala and insula and increasing connectivity between the amygdala and hippocampus, MDMA may enhance a person’s ability to retrieve, approach and emotionally engage with, process and reconsolidate traumatic memories and facilitate fear extinction.^29^ These mechanisms, while not specifically examined in the current trial, are key to the effectiveness of exposure therapy and are particularly challenging for individuals with comorbid AUD. Clinical trials examining the efficacy of MDMA-assisted therapy for PTSD suggest that MDMA-assisted therapy could be a promising candidate for augmenting treatment outcomes for individuals with PTSD.^31^ MDMA is administered in a controlled clinical setting as an adjunct to psychotherapy, combining preparatory sessions, dosing sessions and integration sessions. Integration sessions most often occur the day following dosing (sometimes referred to as the ‘therapeutic window’), with the aim of processing insights, emotions and memories that arose during the dosing session. With regards to AUD, there has been just one open-label pilot study investigating MDMA-assisted therapy in 14 patients with AUD which reported that MDMA was well tolerated and reduced self-reported alcohol consumption^32^ in addition to reduced cravings and improved sleep.^33^ However, the small sample, lack of a control group and objective outcomes indicate that these findings are exploratory and require further replication. Taken together, there is solid rationale and emerging clinical data suggesting that MDMA-assisted therapy could be of therapeutic benefit for individuals suffering from these disorders concurrently.

Accordingly, we aim to conduct a world-first double-blind RCT of an evidence-based integrated exposure therapy+MDMA for the treatment of comorbid PTSD+AUD: The MDMA-assisted PTSD and Alcohol Therapy Trial (MPATHY). We aim to address well-documented concerns pertaining to the methodological designs associated with the psychedelic-assisted therapy literature^34^ by including an active control, prospective stratification for expectancy and utilisation of evidence-based therapeutic modalities for comorbid PTSD+AUD as the ‘base’ therapy. Indeed, this will be the first randomised double-blind controlled trial of MDMA-assisted therapy that uses a therapy that has well-documented effectiveness for this specific comorbidity (ie, COPE).

We hypothesise that in participants with comorbid PTSD+AUD, MDMA-assisted integrated exposure therapy relative to active control-assisted integrated exposure therapy will: (1) significantly reduce the severity of PTSD symptoms; (2) significantly reduce alcohol consumption; (3) significantly improve depression, insomnia and quality of life; (4) yield good treatment satisfaction and engagement; (5) have minimal adverse events (AEs) and (6) be cost-effective. This article presents the protocol for the RCT and is written to comply with the recommended Standard Protocol Items: Recommendations for Interventional Trials (SPIRIT) guidelines for RCT protocols.^35^

## Methods

### Study objectives

This is a double-blind RCT to examine the effectiveness of MDMA-assisted COPE therapy versus active control-assisted COPE therapy in improving treatment outcomes for individuals with PTSD+AUD.

### Study design

This study is a parallel-group RCT conducted at two clinical sites. Following consent, pre-treatment screening and assessment, and randomisation, participants will receive 12 sessions of integrated exposure therapy (COPE) and two dosing sessions (MDMA or control) at visits 5 and 12. Each dosing session is preceded by a preparatory session the week prior and followed by an integration session the day after. Thus, participants in both arms may receive up to 18 sessions of therapy in total (see figure 1). Follow-up visits will occur at the final COPE session (end of treatment), and 6 and 12 months after baseline. The design follows Good Clinical Practice, Consolidated Standards of Reporting Trials and SPIRIT guidelines.

**Figure 1 F1:**
[figure not shown]
Flow chart of trial procedure for a double-blind RCT of an evidence-based integrated exposure therapy+MDMA for the treatment of comorbid PTSD+AUD. The MDMA-assisted PTSD and Alcohol Therapy Trial (MPATHY). AUD, alcohol use disorder; COPE, Concurrent Treatment of PTSD and Substance Use Disorders Using Prolonged Exposure; M, month; MDMA, 3,4-methylenedioxymethamphetamine; PTSD, post-traumatic stress disorder; RCT, randomised controlled trial.

### Participant recruitment

The trial is being conducted in two outpatient hospital and community settings in New South Wales (NSW) and Victoria (VIC), Australia. The trial is now in the recruitment phase (expected completion: 2027). We aim to recruit participants through clinical referral (from treating clinicians of participating hospitals and community clinics) and via flyers/community advertisements in general practices, newspapers, websites and social media (eg, Facebook). Based on our previous experience, recruitment from mixed sources does not significantly impact treatment retention or outcome in alcohol trials.^36^ Participant time and travel expenses are reimbursed at the follow-up research assessments.

### Randomisation and allocation concealment

The study is a double-blind, RCT with participants randomised to receive one of two possible medication arms, in addition to COPE therapy. The study is conducted under double-blind conditions so that participants and study staff are unaware of medication assignment. A computer-generated random allocation to MDMA or active control (niacin) will be provided by an independent service and conducted in a secure web-based database (RedCap software) and stratified for balancing by site (NSW vs VIC), sex at birth (male vs female), prior MDMA use (Y/N), prior selective serotonin reuptake inhibitor use (Y/N), PTSD severity (PTSD checklist for DSM-5 (PCL-5): >47), trauma (multiple vs single) and treatment expectancy (positive vs negative, Stanford Expectations of Treatment). This information is provided to the Clinical Trial Pharmacists at each site for intervention allocation and medication dispensing. In the event of a medical emergency that requires knowledge of the treatment condition, the investigators can contact the pharmacist to break the randomisation code for that individual.

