### Sample size calculations

This study is sufficiently powered to estimate the effects of COPE+MDMA versus COPE+Control on significant reductions in clinician-administered PTSD symptom severity over time (CAPS-5). For the COPE+Control, based on our previous COPE trial^17^ we assume a 26% reduction in CAPS-5 score from baseline to treatment completion (Week 14) and a 42% reduction from baseline to longer follow-up. For COPE+MDMA, based on prior work of MDMA-assisted therapy,^71 72^ we assume a 55%–63% reduction from baseline. We consider these estimated separations of CAPS-5 data over repeated measures. To achieve >80% power for a two-sided test at α=0.05 conservatively assuming a within-participant correlation of 0.5 and 15% data loss, based on prior studies,^47^ 50 participants will be needed per arm (active vs control) (n=100) for the effect of MDMA versus control, time and treatment×time where the groups separate to a medium to large effect (f=0.25, Cohen’s d=0.5–0.7).

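### Seven two-level stratification factors for 100 participants make 128 strata if fully crossed, so the scheme gives only weak balance, including on the treatment expectancy offered as a bias safeguard

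*Protocol article*

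**What the plan says.** Under Randomisation and allocation concealment, an independent service generates the allocation in a web-based database. It is "stratified for balancing by site (NSW vs VIC), sex at birth (male vs female), prior MDMA use (Y/N"), then "prior selective serotonin reuptake inhibitor use (Y/N), PTSD severity (PTSD checklist for DSM-5 (PCL-5): >47), trauma (multiple vs single"), and finally "treatment expectancy (positive vs negative, Stanford Expectations of Treatment"). Each of the seven factors has two levels (PCL-5 severity through a single cut-off).

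The Abstract says that the trial "will aim to randomise 100 participants with PTSD+AUD". Sample size calculations gives the same total: "50 participants will be needed per arm (active vs control) (n=100").

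The strengths list says that bias is minimised by the randomised, blinded design together with the "inclusion of an active control and prospective stratification for expectancy". The end of the Introduction and the Discussion repeat stratification for expectancy as an answer to the methodological faults of earlier trials. The article does not mention minimisation, dynamic allocation, block size or a reduced set of strata.

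Statistical analysis compares the arms with mixed models and assigns additional covariates to sensitivity analyses. It does not say that the allocation factors enter the primary model.

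**The concern.** Stratification balances a factor only when strata fill enough for their blocks to complete. With more strata than participants, most occupied strata hold one or two people. The blocks stay open and allocation moves back towards simple randomisation. Adding factors therefore weakens the balance on every one of them, expectancy included.

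This matters more here than in most trials. The Discussion lists strong expectancy effects and small samples among the faults of earlier MDMA studies, and offers stratification for expectancy as part of the remedy. A reader would expect the arms to be closely matched on expectancy by design. As written, the scheme does not provide that.

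**Working it through.** **Inputs.** Seven factors at two levels each (Randomisation and allocation concealment); N = 100, 50 per arm (Sample size calculations). The article gives no stratum count, so there is no figure of that kind to reproduce. N = 100 is consistent with its own inputs (f = 0.25, correlation 0.5, 15% loss, 80% power). A between-group repeated-measures F test needs 86 participants with three measures (86/0.85 = 101.2, so 102) or 82 with four (82/0.85 = 96.5, so 97). The number of measures is an assumption and does not affect this point.

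**Strata.** 2^7 = 128. Participants per stratum: 100/128 = 0.78, or 0.39 per arm.

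**Occupancy, all prevalences 50%.** Expected empty strata: 128 × (127/128)^100 = 58.4, so about 70 are occupied. Expected strata with one participant: 100 × (127/128)^99 = 46.0. By simulation, about 69 of the 70 occupied strata hold fewer than four people and cannot complete a block of 4.

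**Other prevalences.** Order: site, sex, prior MDMA, prior SSRI, severity, trauma, expectancy.
- Moderate set (50/50/40/70/50/80/70%): 57 strata occupied, 33 with one person, 53 with fewer than four.
- Skewed set (50/60/30/80/40/90/85%): 42 occupied, 22 with one person, 34 with fewer than four.

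**Balance.** Simulation of 1,500 trials per setting, N = 100, factors independent. Entries are equal / moderate / skewed prevalences. The gap is the difference between arms in the percentage with positive expectancy.

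| Allocation | SD of gap (points) | Gap ≥10 points | Any of the 7 factors ≥15 points apart | Arms 55:45 or worse |
|---|---|---|---|---|
| Simple | 9.96 / 9.21 / 7.05 | 32 / 27 / 16% | 63 / 57 / 48% | 40 / 36 / 37% |
| Seven-factor strata, blocks of 4 | 8.70 / 7.64 / 6.19 | 25 / 19 / 10% | 45 / 31 / 12% | 30 / 24 / 18% |
| Seven-factor strata, blocks of 2 | 7.20 / 6.59 / 5.29 | 17 / 13 / 6% | 21 / 14 / 4% | 21 / 16 / 10% |
| Minimisation, 80% biased coin | 4.56 / 4.51 / 4.19 | 5 / 3 / 2% | 4 / 4 / 4% | 0% |

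Analytic check of the first row: SD = 100 × √[p(1−p)(1/50 + 1/50)], which is 10.0, 9.2 and 7.1 points for p = 0.5, 0.7 and 0.85. The normal chance of a gap of 10 or more is then about 32%, 28% and 16%. Gaps of exactly 10 points are common when the arms are equal, and repeat runs put the simple figure as high as about 35% and the minimisation figure between about 1% and 5%.

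**Gain over simple randomisation in the SD of the gap.**
- Blocks of 4: 1 − 8.70/9.96 = 13%, 1 − 7.64/9.21 = 17%, 1 − 6.19/7.05 = 12%.
- Blocks of 2: 28%, 28%, 25%.
- Minimisation: 54%, 51%, 41%.

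**Fewer strata.** Crossing only site, PCL-5 severity and expectancy (8 cells) gives an SD of about 2.5 to 2.7 points and almost no gaps of 10 under equal or moderate prevalences. Some factor among the seven still differs by 15 points or more in about 36 to 42% of trials, because four of them are left free.

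**The case against.** **The mechanism is not spelled out.** The article does not say that the factors are fully crossed in permuted blocks, and block size is a detail that it may leave to the full protocol. This stands as a condition on the figures. It does not remove the point: the factor list and the word 'stratified' are published. If minimisation is in use, the description needs correcting.

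**The scheme does some good.** This stands. A reader might infer that seven-factor stratification cannot balance anything. The simulation contradicts that: every measure improves on simple randomisation, most clearly with blocks of 2.

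**The primary result is not undermined.** A reader might also infer a biased test. The documents do not support that: sparse strata leave randomisation valid. If expectancy groups differed by 0.3 to 0.8 SD in outcome (assumed), a 15-point gap would shift the contrast by 0.15 × 0.3 = 0.045 to 0.15 × 0.8 = 0.12 SD, against a planned d of 0.5 to 0.7. A 45:55 split keeps 4 × 0.45 × 0.55 = 99% of efficiency, so the drift in arm sizes matters little.

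**Balancing baseline expectancy does not cure unblinding.** This stands as well. Bias from a broken blind arises after allocation. The article deals with it separately, through checks of guessed allocation (Medications) and blinded independent CAPS-5 raters (Outcomes). It is a further reason to word the safeguard claim modestly.

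**Analysis can repair chance imbalance.** This is true, and the analysis plan, which is not shown, may provide for it. The article itself places additional covariates in sensitivity analyses and treats expectancy as a predictor of response.

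**Conclusion.** The point holds as a weakness of design. If the seven factors are crossed as 'stratified' implies, there are 128 strata for 100 participants, and balance on any one factor is weak. Under equal or moderate prevalences, an expectancy gap of 10 points or more occurs in about 20 to 25% of trials with blocks of 4 and 12 to 17% with blocks of 2. Simple randomisation gives about 27 to 35% and minimisation about 1 to 5%. Under the skewed set the figures fall to about 10%, 6%, 16% and 2%, with the same ordering.

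The figures rest on assumed prevalences, independent factors and crossed permuted blocks. The stratum count rests on the article alone. The expectancy safeguard is delivered only in small part, while the validity of the allocation and of the test is untouched. It should be fixed.

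**What to change.** 1. For the remaining participants, balance the seven factors by minimisation on the margins with a random element (for example, 80% to the arm that improves balance). The independent service should take the existing allocations into account centrally, so that concealment is kept. If minimisation is already in use, replace 'stratified' under Randomisation and allocation concealment with a correct description. Crossing fewer factors is the alternative, but it protects only those retained.
2. In either case, include the allocation factors in the primary mixed model, at least site, baseline PTSD severity and expectancy, and not only in sensitivity analyses.
3. Reword the strengths list, the end of the Introduction and the Discussion so that they claim no more than improved baseline balance on expectancy.

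Cost: a centrally hosted algorithm, an amendment part-way through recruitment, and two allocation regimes to describe in the report. Allocation is already central and web-based, and no extra participants or visits are needed. Items 2 and 3 cost only text.
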